##### Secondary outcomes

The secondary otucomes are: (1) the number of people per 10,000 (rate) attending the triage post without any eye condition (false positives) as determined by the eye team; (2) the number of people per 10,000 population (rate) attending KEU within four weeks after being referred from PHC; (3) the proportion of participants referred from the PHC who attend the referral at KEU within four weeks of being referred from a PHC; and (4) the time taken by a participant referred from PHC to attend KEU.

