#### Assignment of interventions

##### Allocation

There are 66 potentially eligible CUs in the county (see above). We will select 36 CUs for inclusion in the trial. In order to ensure balance between the arms, restricted randomisation will be used. A list of the 66 CUs with their sub-county, distance from Kitale and direction from Kitale (categorised into four quadrants, North, South, East and West) will be compiled and used during randomisation. A statistician, who will not participate in recruitment, will generate a random allocation sequence. Randomisation will consider the direction, cluster size and distance from the hospital. The following restrictions will be used in the randomisation:each arm must include at least two CUs from each sub-county;each arm must include at least two CUs from each direction of North, South, East and West;the ratio between number of CUs in each arm from each direction must be in the range of 0.67–1.5;the difference in mean health centre distance from Kitale in each of the arms should not be > 4 km; andthere should not be more than one CU per link health facility.

A list of 10,000 valid permutations will be generated and checked that there are no clear deviations in randomness (e.g. pairs of health centres that occur within the same arm considerably more/less often than would be expected by chance). One of these 10,000 permutations will be computer-selected at random. A list of CUs allocated to the control group, intervention group and those not involved will be prepared.

In health facilities where there are larger catchment populations and served by more than one CU, one of the CUs will be randomly selected along with its population unit, so that the size of the clusters studied is around 5000.

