#### Analysis of secondary outcomes

The proportion attending triage but having no eye condition (false-positive attendance rate) will be estimated in a similar manner to the above in both arms, with a rate difference estimated, along with its 95% CI.

In order to estimate the effect of the intervention on the attendance rate of true positives at KEU the approach will be identical to the cluster-level analysis of the primary outcome. The numerator of each cluster is the number of individuals attending KEU following a referral from triage and the denominator is the cluster population. Again, a t-test will be used to assess the evidence as to whether the rate differs between arms and the analysis will again be unadjusted.

The difference in the proportion of patients referred from the PHC to the KEU who attend their referral within four weeks, by arm, will be tested using a random effects logistic regression, with attendance at KEU as the outcome, trial arm as the primary exposure and cluster as a random effect to account for within cluster correlation. Due to the fact that the characteristics of the patients referred in each arm may be different (due to the potential upstream impact of the intervention), this analysis will be adjusted for sex, age group and distance from KEU.

The impact of the intervention on time-to-attendance will be investigated, using Kaplan–Meier plots for each arm to compare attendance of referral. The hazard ratio will be estimated using Cox regression, again adjusted for sex and age group, to assess whether patients referred in the intervention arm attended their referrals sooner than those in the control arm..

We will assess possible effect modification of sex, age and distance from KEU. In the cluster-level analyses, the approach recommended by Cheung et al. [53], will be used for age and sex, where the rate in each group within each cluster will be estimated, then the difference in this rates in each group found, before finally performing a t-test on these differences by arm. In order to identify if the distance from KEU is an effect modifier, since it is a cluster-level covariate, this can be done by performing a linear regression on the cluster level rates and include distance and trial arm as exposures with an interaction term between them. For the individual-level analyses, an interaction term will be included with trial arm for each of the potential effect modifiers (age, sex, distance from KEU).

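### The Cox model for time to attendance at KEU omits distance, although the logistic model for attendance in the same referred patients adjusts for it and the stated reason covers both

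*Protocol article*

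**What the plan says.** All references are to the protocol article.

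Secondary outcomes lists, third, "the proportion of participants referred from the PHC who attend the referral at KEU within four weeks" and, fourth, "the time taken by a participant referred from PHC to attend KEU". Both follow patients referred from primary care to KEU, and both count arrival at KEU as the event.

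Analysis of secondary outcomes plans a random-effects logistic regression for the third outcome. It gives a reason for adjusting, namely that "the characteristics of the patients referred in each arm may be different (due to the potential upstream impact of the intervention", and concludes that "this analysis will be adjusted for sex, age group and distance from KEU". For the fourth outcome it says: "The hazard ratio will be estimated using Cox regression, again adjusted for sex and age group". For effect modification in the individual-level analyses, "an interaction term will be included with trial arm for each of the potential effect modifiers (age, sex, distance from KEU".

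Allocation restricts the randomisation so that "the difference in mean health centre distance from Kitale in each of the arms should not be > 4 km". Data analyses counts distance from hospitals among the baseline variables to be compared between arms as potential confounders.

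**The concern.** The word 'again' in the Cox sentence points back to the adjustment just described, but one of its three covariates has gone. The reason for adjusting concerns who gets referred, and that group is the same in both analyses. Distance is also the listed covariate with the plainest link to how soon a patient can reach KEU.

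The hazard ratio is meant to show whether Peek patients attend sooner. If the referred patients in one arm live further from KEU on average, and distance slows attendance, part of the hazard ratio would reflect geography. The logistic result would have that part removed, so the two analyses could differ for a reason unrelated to Peek.

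**Working it through.** **1. The two models side by side**

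| | Third secondary outcome | Fourth secondary outcome |
|---|---|---|
| Patients | Referred from primary care | Referred from primary care |
| Event | Attended KEU within four weeks | Attended KEU (time to) |
| Model | Random-effects logistic | Cox |
| Cluster term named | Yes | No |
| Covariates | Sex, age group, distance | Sex, age group |
| Reason for the covariate set | Referred patients may differ by arm | None for dropping distance |

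**2. The plan's own design figure**

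The only design figure is for the primary outcome. With rates of 1.5% and 2.0%, 90% power and two-sided 5%, n per arm = (1.960 + 1.282)² × (0.015 × 0.985 + 0.020 × 0.980) / 0.005² ≈ 14,450. The design effect is 1 + 4,999 × 0.001 = 5.999. Clusters per arm = 14,450 × 5.999 / 5,000 ≈ 17.3, rounded up to 18, with power 91.0%. This reproduces the stated 18 per arm. It says nothing about the Cox analysis, for which the document gives no event count, variance or distance effect. All inputs below are therefore assumptions.

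**3. Shift in the hazard ratio when distance is omitted**

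Let h be the hazard ratio per km further from KEU and g the gap in mean distance among referred patients (Peek minus control). Then, approximately, hazard ratio without distance = true hazard ratio × h^g.

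With a true hazard ratio of 1.00:

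| h per km | g = 2 km | g = 4 km |
|---|---|---|
| 0.99 | 0.99² = 0.98 | 0.99⁴ = 0.961 |
| 0.97 | 0.97² = 0.94 | 0.97⁴ = 0.885 |
| 0.95 | 0.95² = 0.90 | 0.95⁴ = 0.815 |

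A simulation agrees. It used 400 trials per scenario, 18 units per arm, 22 control and 30 Peek referrals per unit, about 50% attending within 28 days, and a distance SD of 8 km. At 4 km the mean hazard ratio without distance was 0.958, 0.884 and 0.820. With distance in the model it was 0.996 to 0.997. If the control arm is further away, the shift reverses.

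A second simulation used a true log hazard ratio of 0.40 (hazard ratio 1.49), 15 referrals per unit and no other between-unit variation. A distance effect of −0.3 per 10 km corresponds to exp(−0.03) = 0.97 per km. Without distance, the log hazard ratio fell to 0.336 (hazard ratio 1.40) at 2 km and 0.275 (1.32) at 4 km. With distance it was 0.403 and 0.404. With no distance effect, omission made no difference at any gap (0.398 to 0.400).

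**4. How large a gap to expect**

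With a unit-level SD of 8 km and 18 units per arm, the SD of the difference in means is 8 × √(2/18) = 2.67 km. Under a normal approximation truncated at ±4 km, ignoring the other restrictions, the mean absolute gap is about 1.7 km. At 0.97 per km that gives 0.97^1.7 ≈ 0.95.

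**5. Width of the interval**

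Second simulation, zero gap, between-unit SD 0.3 on the log hazard; mean standard error of the log hazard ratio:

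| Distance effect per 10 km | Robust, without distance | Robust, with | Naive, without | Naive, with |
|---|---|---|---|---|
| 0 | 0.143 | 0.141 | 0.114 | 0.114 |
| −0.3 | 0.157 | 0.140 | 0.114 | 0.115 |
| −0.7 | 0.208 | 0.142 | 0.114 | 0.115 |

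With a cluster-robust standard error, the interval without distance is 0.157/0.140 = 1.12 or 0.208/0.142 = 1.46 times as wide, if distance is prognostic. With a naive standard error there is no gain.

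**The case against.** The strongest reply is that randomisation already deals with distance. Allocation restricts on distance, direction and sub-county. The 4 km figure is a rejection limit, and the expected gap in unit means is zero. That stands, and it means the 4 km column shows the edge of what is allowed, not a forecast. It does not close the matter. The restriction acts on means over units, whereas both models analyse referred patients, whose spread over units may differ by arm. The protocol accepts this for the logistic model. How far Peek would change that spread is not quantified here, because the first simulation fixed referrals per unit within each arm and the second used the same number in every unit.

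The distance effects are assumed, and the steepest is extreme: 0.95 per km over 32 km (±2 SD) gives 0.95³² = 0.19, a five-fold difference in hazard. That objection stands, so the conclusion rests on 0.97 per km.

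A reader might infer that the planned arm-by-distance interaction obliges the main Cox model to contain distance. It does not. Interaction models are separate from main models, and the protocol follows that pattern for its cluster-level outcomes: an unadjusted main analysis, then a separate regression with distance, arm and their interaction.

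Nor would a shared covariate set make the two results interchangeable. One is an odds ratio at four weeks conditional on cluster; the other is a hazard ratio.

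**Conclusion.** The inconsistency stands as a minor point. Two analyses of the same event in the same patients have different adjustment sets, no reason is given, and the stated rationale supports distance in both.

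The consequence is conditional. A reader might infer that the hazard ratio will carry a distance imbalance. The document does not support that: a shift needs both a gap between arms among referred patients and an effect of distance on attendance, and neither is given. Assuming 0.97 per km and a true hazard ratio of 1.00, the result is about 0.94 at 2 km and 0.88 at 4 km with the Peek arm further away, and the opposite with the control arm further away.

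A reader might also infer that the interval is too wide as planned. That holds only with a cluster-robust standard error and a prognostic distance effect. The Cox sentence does not name its variance method, and with a naive standard error adding distance leaves the width the same or slightly larger.

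One secondary outcome is affected. The primary analysis and the sample size are not.

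**What to change.** In Analysis of secondary outcomes, make the Cox regression adjust for sex, age group and distance from KEU, with distance coded as in the logistic model. If the omission is deliberate, state the reason instead. Settle this before the attendance data are analysed, so that the adjustment set is not chosen with results in view.

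The cost is one phrase in the text and one more parameter in the model if distance enters as a linear term. No new data are needed: Allocation already has distance from Kitale compiled for every candidate community unit, and the logistic model already uses distance from KEU. The hazard ratio will then be conditional on distance, as the odds ratio already is.

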#### Cluster definition

The unit of randomisation for this trial will be Community Units (CU). These are defined as a dispensary or health centre together with the community they serve (Fig. 2). A typical CU comprises a population of 5000–10,000 people. It has a dispensary or health centre, staffed by one or two Community Health Extension Workers (CHEWs). Associated with each CU, there are usually 20–50 CVs [47]. The CHEWs based at the health centre or dispensary train, support and supervise the CVs. To date, 85 CUs have been established and personnel trained in this county [46]. CUs were chosen because it represents the future shape of healthcare in Kenya; they are distributed throughout the county and have a good referral network that provides linkages between community and health system. The CUs with untrained personnel provide a buffer zone that will minimise contamination.

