#### Sample size

The sample size of 36 clusters was determined using the Hayes formula for rates in unmatched cluster randomised trials [49]. In Trans Nzoia County, a typical health facility has a catchment population of 5000 people [46]. During previous community outreaches to these health facilities, about 50–100 new patients attended. This translates to an average rate of 15 per 1000 population [50]. Assuming an intraclass correlation coefficient of 0.001, desired power of 90% and significance level of 5%, a sample of 36 CUs (18 in each arm) would be sufficient to detect a difference of 0.5%, from 1.5% in the control arm to 2.0% in the intervention arm (a 33% relative change) in overall attendance rates.

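### The Cox model for time to attendance at KEU has no term for clustering by community unit, so its interval is too narrow and its test rejects too often

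*Protocol article*

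**What the plan says.** The unit of randomisation is the community unit (Protocol article, Cluster definition), with 18 CUs in each arm (Sample size). The fourth secondary outcome is the time a patient referred from the PHC takes to attend KEU (Secondary outcomes).

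Under Analysis of secondary outcomes, the model for that outcome is: "The hazard ratio will be estimated using Cox regression, again adjusted for sex and age group". The stated aim is to see whether referred patients in the Peek arm attend sooner than those in the control arm. Kaplan–Meier plots by arm accompany it.

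One paragraph earlier, the logistic model for the proportion of the same referred patients who attend KEU has "cluster as a random effect to account for within cluster correlation". The article gives a reason for covariates there, namely that the mix of referred patients may differ by arm, and states that "this analysis will be adjusted for sex, age group and distance from KEU". The primary outcome and the two secondary rates are analysed from cluster-level rates.

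**The concern.** Four of the five listed outcomes have an analysis that respects the randomisation by CU. Time to attendance is the exception. Followed as written, the model treats patients from 36 CUs as independent.

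They are not independent. Patients from one CU share a link facility, a triage clinic on one date, the same one or two CHEWs and essentially the same distance to KEU. In the Peek arm, the list of non-attenders goes to the responsible CHEW, so part of the follow-up is itself delivered by cluster.

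The covariate list also changes without explanation. The wording suggests the same adjustment is repeated, yet distance from KEU is dropped. The article's reason for adjusting the logistic model applies equally to a Cox model on the same patients, and distance is a plausible driver of how soon they attend.

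At stake is a claim that Peek brings patients to hospital faster, resting on an interval that is too narrow.

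**Working it through.** **1. The article's own figure.** No figure is given for the time-to-attendance analysis. The sample size for the primary outcome does reproduce. Inputs (Sample size): rates "from 1.5% in the control arm to 2.0% in the intervention arm (a 33% relative change) in overall attendance rates", 5000 people per CU, ICC 0.001, 90% power, 5% significance (taken as two-sided).

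- Individually randomised: 14,451 per arm.
- Design effect: 1 + (5000 − 1) × 0.001 = 5.999.
- CUs per arm: 14,451 × 5.999 / 5000 = 17.3, so 18, with power 91.0%.

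The design therefore allows for clustering in the primary outcome; the Cox model does not.

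**2. Direction.** Arm is constant within a CU. With n patients per CU and intraclass correlation ICC, the variance of the arm effect is multiplied by about DE = 1 + (n − 1) × ICC. The true standard error is √DE times the reported one, and the true level of a nominal 5% test is 2 × [1 − Φ(1.96/√DE)].

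**3. Size.** The article gives neither the number referred to KEU per CU nor the ICC among referred patients. Both are assumptions here. The 50–100 patients seen at past outreach clinics (Sample size) are a guide to how many could be referred per CU.

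| Referred per CU | ICC | DE | True SE / reported SE | True level |
|---|---|---|---|---|
| 20 | 0.001 | 1.02 | 1.01 | 5.2% |
| 20 | 0.01 | 1.19 | 1.09 | 7.2% |
| 20 | 0.02 | 1.38 | 1.17 | 9.5% |
| 20 | 0.05 | 1.95 | 1.40 | 16.0% |
| 30 | 0.001 | 1.03 | 1.01 | 5.3% |
| 30 | 0.01 | 1.29 | 1.14 | 8.4% |
| 30 | 0.02 | 1.58 | 1.26 | 11.9% |
| 30 | 0.05 | 2.45 | 1.57 | 21.0% |

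For ICC 0.02–0.05 the standard error is understated by 1 − 1/√1.38 = 15% to 1 − 1/√2.45 = 36%.

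**4. Simulation of the Cox model itself.** The design-effect formula is not specific to censored data, so it was checked by simulation under no arm effect. There were 18 + 18 CUs, log-normal CU frailty, censoring at 28 days, arm as the only covariate and 2000 trials per setting. With an average of 20 patients per CU and a baseline 50% attending by day 28:

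| Frailty variance | Empirical SD of log HR | Mean model SE | Rejection, plain Cox | Rejection, cluster-robust |
|---|---|---|---|---|
| 0 | 0.105 | 0.106 | 4.8% | 5.0% |
| 0.05 | 0.128 | 0.105 | 10.2% | 5.0% |
| 0.10 | 0.145 | 0.105 | 15.9% | 4.3% |
| 0.25 | 0.184 | 0.105 | 27.2% | 3.9% |

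The formula tracks this. Frailty variance 0.05 corresponds to an ICC of about 0.023 for attendance by day 28, so DE = 1 + 19 × 0.023 = 1.44 and the level is about 10%.

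Over 10–40 patients per CU and 30–50% attending, plain Cox rejects in 6.7–38.9% of trials for frailty variances 0.05–0.25. The cluster-robust test (36/34 correction, t with 34 degrees of freedom) stays at 3.9–6.0%.

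**5. A reference point from the article.** ICC 0.001 at a 1.5% rate implies a between-CU coefficient of variation of √(0.001 × 0.985 / 0.015) = 0.256, or a frailty variance of about 0.256² = 0.066. If between-CU variation in the KEU attendance hazard were similar, the relevant settings are 0.05 and 0.10, which give about 7–24% over the same range.

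**The case against.** The strongest reply is that the article is silent on the variance, and silence is not a statement of independence. It condenses a fuller document, the authors clearly understand clustering, and a variance estimator for the last of four secondary outcomes could be left to an analysis plan. An unseen plan may well supply the term. But the article does specify this model and its covariates, right after naming the cluster term for the neighbouring model. No other sentence fills the gap: Data analyses cites the CONSORT cluster extension for reporting only, and the later sentence on individual-level analyses adds only interactions.

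The size is assumed throughout, and the only ICC in the article, 0.001, would make the inflation negligible (5.2–5.3%). This stands as the lower end of the range. However, that value describes a 1.5% rate in whole populations, and there is no reason for it to hold for attendance among referred patients.

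On distance, the restricted randomisation caps the difference in mean facility distance between arms at 4 km, and distance does enter the planned interaction analyses. Both points soften this part. Still, the restriction balances facilities, not the patients who end up referred, and the main hazard ratio remains unadjusted for distance.

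Finally, the primary outcome is untouched, and attendance within four weeks is analysed with a cluster random effect. Both are true, and they limit the problem to one secondary outcome.

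**Conclusion.** The concern holds. As written, the Cox analysis of time to attendance is not valid for a trial that randomises CUs. The direction is certain if within-CU correlation is positive: the interval for the hazard ratio is too narrow and the test rejects too often.

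The size cannot be fixed from the article. Assuming 20–30 referred patients per CU and an ICC of 0.02–0.05, the true level is 9.5–21%; at 0.01 it is 7–8%, and at 0.001 there is almost no inflation. Omitting distance from KEU is a lesser, related fault: it is inconsistent with the logistic model and leaves explainable between-CU variation in the residual.

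**What to change.** State in advance that the Cox model will either use a variance clustered on CU, with a small-sample correction for 36 clusters, or include a shared frailty for CU. Choose one, because they estimate different quantities: the first gives a marginal hazard ratio, the second one conditional on the CU. The frailty is the closer analogue of the logistic random effect; the corrected cluster-robust variance is the option checked above. Adjust for sex, age group and distance from KEU, as in the logistic model. Keep the Kaplan–Meier plots as description, and apply the same clustering method to the Cox interaction models.

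The cost is one sentence in the analysis plan and one option in Stata. No new data or change in trial conduct is needed. The interval will widen to reflect the design.

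If an analysis plan already contains the term, confirming that and citing it settles the clustering point.

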### Monitoring

#### Data monitoring

The study presents minimal risk and we do not anticipate significant adverse events. Therefore, a data and safety monitoring committee was not considered necessary; however, an audit will be done by the London School of Hygiene and Tropical Medicine (LSHTM), the Trial Sponsor, if it is deemed necessary. No interim analysis is planned due to the relatively short duration of the study.

